**Fig. 1 Fig1:**
[figure not shown]
Intervention Effects on Use of Hearing Conservation Strategies

Although hearing conservation programs for farm and non-farm youth have been successful in changing hearing protector use, [5, 25, 27–30] effectiveness of programs is limited by lack of reach to at-risk youth, and effective doses [25, 28, 30]. The proposed study uses an established educational system (Safety Day) to deliver hearing health education to youth, and will determine the most effective and sustainable approach to hearing health education among farm and rural youth.

This project will result in identification of the effectiveness, costs, and sustainability estimates associated with each approach to hearing health education among farm and rural youth. Cost-effective and sustainable hearing health education programs are expected to have the greatest impact on reducing rates of noise-induced hearing loss, tinnitus, and other negative effects of high noise exposure, and improving quality of life in this high-risk and underserved group.

This study maximizes opportunity for a sustainable impact on public health by building on a well-established educational program, Safety Day. Ongoing activities in the Safety Day (exclusive of this study) include recruiting, training, and administering consents; the study activities will incrementally increase activities in these areas, leading to a high level of efficiency.

The proposed study tests an under-tested intervention approach: the booster. Previous randomized clinical trial (RCT) studies examining the use of boosters on hearing protector use [31, 33, 34] have had ambiguous results, pointing to the need for further study of this promising approach.

The proposed study addresses long-standing problems with hearing health education programs which have not been addressed by previous effectiveness studies, i.e., access and program sustainability. The proposed study also uses a previously-established, tested, [28] free-to-use Internet program (Dangerous Decibels® virtual exhibit) not previously tested for use among farm and rural youth.

The proposed study uses a strong (RCT) scientific design. Information from this stronger study design will provide more generalizable evidence useful in the future development of hearing conservation programs and health policy, resulting in enhanced opportunity to impact the public’s health.

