## Methods and design

A team of multidisciplinary members with diverse expertise has been formed to accomplish the study aims. Areas of expertise include: 1) development and testing of programs designed to increase use of hearing protection devices among farmers, 2) farm youth safety education, 3) analysis of hearing health education programs, 4) health program cost analysis, 5) assessment of public health program sustainability, and 6) Web hosting and user monitoring.

The purpose of this project is to compare the effectiveness and sustainability of new programs designed to increase hearing conservation practices (e.g., use of HPDs, turn it down, walk away) among farm and rural youth, thereby reducing noise-induced hearing loss, and involves a partnership with the Progressive Agriculture Foundation. Specifically, the study uses a cluster randomized-control design to compare two programs (with a control) for effectiveness and sustainability: a community-based interactive youth educational program alone (Group A); and a community-based interactive youth educational program followed by an Internet-based booster (Group B). Both programs will be delivered through the Progressive Agriculture Foundation (PAF) Safety Day program.

Safety Days are one-day, hands-on workshops that teach farm children safe farm practices. Each year, Safety Days reach more than 98,000 children and adults in over 400 sites across the United States and Canada. These fun, interactive, and hands-on learning experiences result in increased knowledge about safety, as well as positive change in safety behavior [35–38]. The intervention will also use the Dangerous Decibels® virtual exhibit (DDVE) an Internet-based educational program *targeted to youth* offered through Oregon Health Sciences University and partners. The DDVE will be used as *a* booster in the proposed study.

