#### Setting and procedures

The study will take place through selected sites of a pre-existing system of community-based safety programs for farm and rural youth (Progressive Agriculture Safety Day). Local Safety Day programs will serve as clusters.

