#### Cost

The cost of implementing the program will be based on data associated with program personnel, instructional materials, and travel incurred with the educational process.Personnel (coordinators, instructors, youth): We will estimate hearing education program personnel costs beyond those already incurred through previously established Safety Day programs, i.e., youth, coordinator, and instructor time.Instructional materials: We will value all materials used to implement the lesson (e.g., sound meters, printed supplies), including lesson development costs and youth time on public-access or home-based computers.Travel: We will estimate travel costs incurred by coordinators, instructors, and youth to participate in pre-program training and the local Safety Day program.

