#### Aim 2 will compare program costs

Costs in dollars (e.g., material, travel) will be summarized using mean and standard deviation for each site. Costs in time from volunteers and students will be summarized using mean for each site. At site level, the difference in cost between three intervention groups are compared using one-way analysis of variance. If the effectiveness of intervention is significant, the costs to effective ratio will be calculated to quantify incremental cost of effectiveness.

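### Personnel are costed as an addition to the existing Safety Day but travel to the event is costed in full, so the Aim 2 site costs mix two bases and overstate what the hearing lesson adds

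*Protocol article*

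**What the plan says.** The Cost section of the protocol article names three components: personnel, instructional materials and travel.

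- **Personnel** has an explicit limit: "We will estimate hearing education program personnel costs beyond those already incurred through previously established Safety Day programs". The people covered are youth, coordinators and instructors.
- **Travel** covers the same three groups and has no such limit: "We will estimate travel costs incurred by coordinators, instructors, and youth to participate in pre-program training and the local Safety Day program".
- The opening sentence of the section describes travel more loosely, as "travel incurred with the educational process".

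Under Aim 2 in the statistical analysis, costs are summarised for each site and compared across the three groups by one-way analysis of variance. If effectiveness is significant, the "costs to effective ratio will be calculated to quantify incremental cost of effectiveness".

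The article is clear that the event does not depend on the study. The setting is "selected sites of a pre-existing system of community-based safety programs for farm and rural youth". The text following Figure 1 says of recruiting, training and consent that "the study activities will incrementally increase activities in these areas". Methods and design adds that "Safety Days are one-day, hands-on workshops that teach farm children safe farm practices", and the Interventions section gives the hearing lesson 20 minutes.

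**The concern.** The same people on the same day are costed under two rules. The time that a coordinator or child already spends at the Safety Day is excluded, because it would be spent anyway. The trip that brings that person to the Safety Day is included, although it too would be made anyway.

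A site cost built this way is neither the added cost of the hearing lesson nor the full cost of running a Safety Day that contains it. Aim 2 uses it for both the per-site summaries and a ratio that is meant to be incremental. The lesson is short and uses inexpensive materials, so routine travel could be a large share of the reported total. The Discussion presents cost-effectiveness as a purpose of the trial, so an organisation deciding whether to adopt the lesson would read this figure.

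**Working it through.** The article states no cost, travel or cost-effectiveness figure, so there is nothing to reproduce. The check compares the definitions and then works through an illustration with assumed dollar values.

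**Step 1. Definitions side by side**

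| Component | Limited to what is added to the Safety Day? |
|---|---|
| Personnel | Yes, stated |
| Travel to program training | Added by its nature |
| Travel to the Safety Day by youth and coordinators | No limit stated; the trip is made without the lesson |
| Travel to the Safety Day by instructors | No limit stated; added only if the instructor comes solely to teach the hearing lesson |

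**Step 2. Effect on site cost**

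Let I be the truly added cost per site and t the event travel cost per youth. The number of youth per site is 16, from the power section. The reported site cost is I + 16t instead of I, so the inflation is 16t / I. The values of t and I are assumptions.

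| t (assumed) | 16t per site | Inflation if I = $300 | Inflation if I = $100 |
|---|---|---|---|
| $2 | $32 | 11% | 32% |
| $5 | $80 | 27% | 80% |
| $10 | $160 | 53% | 160% |
| $20 | $320 | 107% | 320% |

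**Step 3. Effect on the contrasts between arms**

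- *Event travel recorded in A and B but not in C.* The A − C difference is (I + 16t) − 0 = I + 16t, and B − C is shifted by the same 16t. The effect in the denominator of the ratio does not change. The A-versus-C ratio is therefore inflated by the percentages in Step 2, with I as the added cost of A.
- *Event travel recorded in all three arms.* A − C is (I + 16t) − 16t = I in expectation. There is no bias in A − C or B − C.
- *B − A.* Both arms carry the same 16t in expectation, so it cancels in either case.

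**Step 4. Effect on precision**

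Take travel cost and added cost as independent, and let r be the ratio of their between-site standard deviations (travel over added cost). With travel recorded in both arms of a contrast, its standard error is multiplied by √(1 + r²):

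- r = 0.5: √1.25 = 1.12
- r = 1: √2 = 1.41
- r = 2: √5 = 2.24

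These r values are also assumptions. The comparison rests on 36 sites / 3 arms = 12 sites per arm, so added noise from differences in travelling distance is not trivial.

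**The case against.** The strongest reply is that nothing shows the ratio to be biased. Aim 2 compares site cost across three groups, so Group C is to have a cost, and control sites hold Safety Days too. Collecting full cost in every arm and taking differences is a valid route to an incremental figure. This stands. A reader might infer that the cost-effectiveness ratio will be too high, but the article does not support that, because it does not say how Group C travel is recorded.

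A second reply is that some event travel belongs in the program cost. The Subject sample section defines instructors by their accepting a hearing health teaching assignment, and the 24 planned instructors match the 24 sites in Groups A and B. An instructor who comes only for that lesson makes an added trip. This also stands. It would be wrong to read all event travel as routine; the problem is mainly youth and coordinator travel.

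A third reply is that the section's opening phrase on travel can be read narrowly, and that a condensed article may leave apportionment to a cost form. This is weaker. The sentence devoted to travel names the Safety Day explicitly, and the limit placed on personnel a few lines earlier is not applied to it. The conflict lies between two stated rules and is not a missing detail.

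Finally, the dollar amounts are assumed. The figure of 16 per site is study enrolment, whereas the Child participation section says that children outside the study also receive the lesson, so the costed number could differ. That is correct, and the table in the working shows only how sensitive the result is.

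**Conclusion.** The point holds in a limited form. Followed as written, the Cost section puts personnel and travel on different bases, and the per-site costs of Groups A and B overstate what the hearing lesson adds. That part does not depend on how Group C is handled.

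The consequence for the contrasts with control is conditional. There is upward bias in A − C and B − C if control-arm event travel is not recorded. If it is recorded, there is no bias in expectation but the between-site variance is larger. B − A is unaffected in expectation in both cases.

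The size cannot be taken from the document. In the assumed range it is 11% to 320% of added site cost, or a standard error 1.12 to 2.24 times as large. The issue is minor. It is confined to Aim 2, and the ratio is formed only if the intervention effect is significant. The primary effectiveness analysis is untouched.

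**What to change.** State one basis for all cost components. The simplest change extends the personnel rule to travel: count only travel beyond that already incurred for the existing Safety Day. This keeps travel to program training and event trips by instructors who attend only to teach the hearing lesson. It excludes routine youth and coordinator travel to the event.

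If full-event cost is also wanted, record every component, personnel included, on that basis in all three arms. Report it separately and take the incremental ratio from differences between arms.

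The first option costs one sentence in the Cost section and a shorter cost form, with less data to collect. The second needs the same cost data from Group C sites.

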#### Sustainability

Schell’s [32] tool will be used to assess sustainability of the hearing health education program. The tool consists of 8 domains, each with five items. For example, the program adaptation domain includes an item, “The program periodically reviews the evidence base.” Following Safety Day intervention delivery, program coordinators will respond to an electronic survey, rating each factor for their own site on a 7-point Likert scale anchored with response options, *to a little or no extent* and *to a great extent.*

### Power and sample size justification

The sample size, in particular the number of sites, was determined by power analysis for a mixed model design using Optimal Design software [39]. The number of sites was selected to provide 80 % power to detect an effect of either intervention with effect size *d* of .48 compared to the effect of the control treatment. This is the effect size on intention to use hearing conservation strategies we found in our preliminary study and is just under what Cohen defined as a medium sized effect. Other necessary inputs into Optimal Design were ranges of the average number of students per site and estimates of the intraclass correlation coefficient (ICC), a measure of the tendency of individuals in the same site to have similar (correlated) responses. To determine the number of sites needed, we examined numbers of site ranging from 20 to 80, and a value of the ICC of .10 (which is typical of its value in health education intervention research [40]. We also adjusted for the possibility of 20 % missing posttest data (which we did by reducing the number of individuals per site by that percentage: thus actually testing the number of individuals per site from 16 to 64). These last adjustments increased the number of clusters we needed to include. The result of the power analysis was 80 % power to detect the target effect size with alpha of .05 two tailed if we included 36 sites with an average 16 individuals per site. Thus we have designed the study to include 36 sites (divided equally among the 3 treatments). Assuming each site includes more than 16 individuals, we will have more than 80 % power. Target youth enrollment of 576 is based on these calculations and US Agriculture Census data [41]. Enrollment numbers also include coordinators (n = 36) and instructors (n = 24).

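### The stated 80% power needs about 16 analysed youth at each of 36 near-equal sites, but the enrollment target of 576 leaves about 12.8 per site after the plan's own 20% loss (77.7% power)

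*Protocol article*

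**What the plan says.** All the inputs are in the protocol article, under Power and sample size justification.

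- The aim is "80 % power to detect an effect of either intervention", for an "effect size *d* of .48 compared to the effect of the control treatment", with "alpha of .05 two tailed" and "a value of the ICC of .10".
- The result is 80% power "if we included 36 sites with an average 16 individuals per site", with the 36 sites split equally over three arms. The only site-size input named for the software is a range of average numbers per site.
- The allowance for 20% missing post-test data was made by shrinking the number per site, so that the sizes actually tested ran from 16 to 64.
- The section then says: "Assuming each site includes more than 16 individuals", power will be above 80%.
- The next sentence reads "Target youth enrollment of 576 is based on these calculations" and on agricultural census data.

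Under Statistical analysis, the primary comparison is a linear mixed model with a random intercept for site.

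**The concern.** Two things do not fit together. First, the tested range of 16 to 64 is the loss-adjusted range, so the 16 that yields 80% is a number analysed. The enrollment target multiplies that same 16 by 36 sites, which leaves nothing for the loss the plan has just allowed for. Second, the only sentence that claims a margin assumes that every site exceeds 16, yet the target fixes the mean at 16.

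Beyond this, 16 is described as an average. Local coordinators and their delegates recruit fourth-graders at local Safety Days, so some spread in site size is to be expected. At a fixed mean, spread can only lower power.

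Power is the stated reason for choosing 36 sites. A null result would be read against 80% or more, which the target does not support on the plan's own assumptions.

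**Working it through.** **Inputs from the article.** d = .48 (SD 1); ICC ρ = .10; two-sided α = .05; 36 / 3 = 12 sites per arm, so J = 24 sites in each comparison with control; mean site size m = 16; loss 20%; target 576. **Assumed here:** the CV of site size, since none is given.

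**Step 1: reproduce the stated figure (equal sites).**
λ = J·d² / {4[ρ + (1−ρ)/m]}, noncentral t with J − 2 = 22 df.
m = 16: λ = 24 × .2304 / {4 × (.10 + .90/16)} = 5.5296 / .625 = 8.85, power **81.1%**.
The stated 80% therefore holds, with about one point to spare. With 33 df (all 36 sites in one three-arm model) power is 82.3%. A normal approximation gives 84.5%.

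**Step 2: the target against the loss allowance.**
576 / 36 = 16 enrolled per site; 16 × .80 = 12.8 analysed.
λ = 5.5296 / {4 × (.10 + .90/12.8)} = 5.5296 / .68125 = 8.12, power **77.7%** (22 df), 79.0% (33 df).
Keeping 16 after a 20% loss needs 16 / .80 = 20 enrolled per site, or 720 in all.

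**Step 3: the sentence claiming more than 80%.**
If all 36 sites exceeded 16, total enrollment would exceed 36 x 16 = 576. At the target the condition cannot be met. This step needs no assumed CV.

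**Step 4: unequal site sizes under the planned mixed model.**
Relative efficiency RE = 1 − CV²·L(1−L), with L = m / [m + (1−ρ)/ρ]; λ is multiplied by RE.
m = 16: L = 16/25 = .64, L(1−L) = .2304.
m = 12.8: L = 12.8/21.8 = .587, L(1−L) = .2424.
Example, m = 16 and CV .5: RE = 1 − .25 × .2304 = .9424; λ = 8.85 × .9424 = 8.34; power 78.8%.

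| Assumed CV | 16 analysed, mixed model | 12.8 analysed, mixed model | 16 analysed, conservative design effect |
|---|---|---|---|
| 0 | 81.1% | 77.7% | 81.1% |
| .3 | 80.3% | 76.8% | 78.9% |
| .5 | 78.8% | 75.1% | 75.2% |
| .7 | 76.3% | 72.5% | 69.9% |

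All entries use 22 df. The last column uses the design effect 1 + [(1 + CV²)m − 1]ρ. It ignores the weighting of sites by their information, so it is only a lower bound for the planned analysis.

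With 16 analysed, mixed-model power falls below 80% at a CV of about .35 (about .50 with 33 df). Drawing gamma-distributed site sizes with the matching weights agreed with the formula: 79.6% at CV .4 and 77.7% at CV .6.

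**The case against.** The strongest reply is that the power figure is right on its inputs, and Step 1 confirms this. It is also fair to say that:

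- **Site-size variation.** A reader might infer that ordinary variation by itself takes power below 80%. The documents do not support that. They give no spread, and under the planned random-intercept model a CV of .3 still leaves 80.3% with 16 analysed. Only the conservative design effect makes the loss look large.
- **The conditional sentence.** It is valid as logic: if every site did exceed 16, power would exceed the equal-16 figure. The target is not called a ceiling, and enrollment might run over. This stands, but the sentence is offered as reassurance about a design whose stated target does not meet its condition.
- **Degrees of freedom and approximation.** With 33 df the figure at 12.8 is 79.0%, and a normal approximation gives 81.3%. That approximation is generous with 24 sites. It also puts the plan's own case at 84.5%, further from the stated 80% than the t calculation does.
- **Unclaimed gains.** The model adds demographic covariates for precision, and the power section names no credit for them. That could recover a point or two, but the article gives no figure for it.
- **Retention.** The article cites about 90% retention in previous studies. Loss may prove smaller, but 20% is what the power section adopted.

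**Conclusion.** The point holds in a limited form. The 80% is not an arithmetic error: it is correct for about 16 analysed youth at each of 12 v 12 near-equal sites. What fails is its link to the enrollment target. At 576 enrolled with 20% loss, power is 77.7% with equal sites (79.0% with 33 df), and the claim of more than 80% rests on a condition that the target rules out.

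Unequal site sizes add a smaller loss whose size depends on an assumed CV: at 12.8 analysed, about 1 point at CV .3 and 2.6 points at CV .5. Taken together, the target supports about 75 to 78% for CV 0 to .5 (22 df). These figures rest on the article's d and ICC, take no credit for covariates, and treat the 20% loss as spread evenly over sites. The shortfall is modest, but it affects the number that justifies 36 sites.

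**What to change.** In Power and sample size justification:

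1. Say whether 16 per site and 576 are numbers enrolled or analysed.
2. Restate power for 576 enrolled after 20% loss over a stated CV range with its basis, giving the degrees of freedom used: about 75 to 78% for CV 0 to .5 with 22 df.
3. Delete the sentence claiming more than 80%, or tie it to an enrollment that would satisfy it.
4. If wanted, state a common per-site target so that sites stay near-equal, without truncating larger sites. A cap that smaller sites do not make up would lower total enrollment and discard information.

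The cost is a slightly less favourable stated figure, with no extra youth or sites. An even spread alone does not bring power back to 80%. If the sponsor wishes to keep that figure, the loss allowance implies an average of 20 enrolled per site (720 in all, 144 more than planned), which is a separate decision about recruitment.

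### The enrolment target of 576 uses the per-site number left after loss (36 × 16), so the stated 20% allowance for missing post-test data is dropped; the effect on power is modest

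*Protocol article*

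**What the plan says.** All of this is in the protocol article, under Power and sample size justification.

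- Aim of the calculation: "The number of sites was selected to provide 80 % power to detect an effect of either intervention", with an effect size d "of .48 compared to the effect of the control treatment" and "a value of the ICC of .10".
- Loss: "We also adjusted for the possibility of 20 % missing posttest data". The method was "reducing the number of individuals per site by that percentage: thus actually testing the number of individuals per site from 16 to 64".
- Result: at a two-sided alpha of 0.05, the 80% figure is said to be reached "if we included 36 sites with an average 16 individuals per site". The 36 sites are split equally over three arms, so 12 per arm.
- Enrolment: "Target youth enrollment of 576 is based on these calculations and US Agriculture Census data".
- A further sentence says that power will exceed 80% provided each site includes more than 16 individuals.

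The section also gives a range of 20 to 80, but attaches it to the number of sites examined. It nowhere gives an enrolled number per site other than the one implied by 576.

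**The concern.** The section uses 16 per site in two incompatible senses. In the power calculation it is what remains after the 20% reduction. In the enrolment target it is what is recruited. Both cannot hold if 20% of post-tests are missing.

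At stake is whether the headline enrolment number supports the headline power. A site team or funder reading 576 would take it to include the loss allowance that the same section describes, and it does not. The closing assurance about sites with more than 16 youths misleads in the same way, because it sets an inclusion count against a threshold that applies to youths with post-test data.

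**Working it through.** **Inputs** (all from Power and sample size justification): two-sided alpha 0.05; d = 0.48 for either intervention against control; ICC 0.10; 20% missing post-tests; 36 sites, 12 per arm; 16 per site in the power result; 576 enrolled.

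**Assumptions.** The remaining software settings are not given. I take a comparison of 12 against 12 sites, equal site sizes, d standardised on the total SD, and 2 × 12 − 2 = 22 between-site degrees of freedom.

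**Step 1: what 576 is.** 36 × 16 = 576 exactly. The 16 is the lower end of the range tested after the 20% reduction. The implied number before loss is 16 / 0.8 = 20 per site, or 36 × 20 = 720 youths. The difference from the target is 720 − 576 = 144. The pre-loss 20 per site is an inference from the 20% reduction, because the text ties its 20 to 80 range to the number of sites. That 16 to 64 is the per-site range after reduction is explicit.

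**Step 2: reproduce the plan's 80%.** With m youths analysed per site:

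SE = √[2 × (ICC + (1 − ICC)/m) / 12], noncentrality = d / SE, and power from the noncentral t distribution with 22 df.

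At m = 16: ICC + (1 − ICC)/m = 0.10 + 0.90/16 = 0.15625; SE = √(2 × 0.15625/12) = 0.161; noncentrality = 0.48/0.161 = 2.97; power **81.1%**. This matches the stated 80%, and 36 is the smallest equal three-arm total that reaches 80% at this site size.

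**Step 3: apply the plan's own loss to 576 enrolled.** 576 × 0.8 = 460.8 youths, or 16 × 0.8 = 12.8 per site. Then 0.10 + 0.90/12.8 = 0.1703; SE = √(2 × 0.1703/12) = 0.168; noncentrality = 2.85; power **77.7%**. At 12.8 per site, 80% power is reached at d = 0.494 rather than 0.48.

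| Enrolled per site | Loss | Analysed per site | Power (22 df) |
|---|---|---|---|
| 20 | 20% | 16 | 81.1% |
| 16 | 10% | 14.4 | 79.6% |
| 16 | 20% | 12.8 | 77.7% |

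**Step 4: the sentence on more than 16 individuals.** By this method 80% power needs about 14.8 analysed per site, which at 20% loss is 14.8 / 0.8 = 18.5 enrolled. A site including 17 would have 17 × 0.8 = 13.6 analysed, below that threshold.

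**Step 5: sensitivity to the method.**

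| Method | m = 16 | m = 12.8 |
|---|---|---|
| 12 vs 12 sites, 22 df | 81.1% | 77.7% |
| 12 vs 12 sites, 33 df (three-arm error) | 82.3% | 79.0% |
| Normal approximation with design effect | 84.5% | 81.3% |
| Omnibus three-arm F test | 84.4% | 81.0% |

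The drop is 3 to 4 points in every row. Of these, the 22-df version comes closest to the stated 80% at m = 16.

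**The case against.** Several points can fairly be made on the other side.

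- **Perhaps 16 is the enrolled number.** Then the stated 80% would carry no loss adjustment, against the section's own account. The contradiction would move, not disappear.
- **The target also cites census data.** It does, but 576 is the exact product of 36 and 16, and the same sentence bases it on the power calculation.
- **20% is only a possibility.** This stands as to size. Under Response rate, retention, and missing data, the article cites earlier retention of 90% at 6 months and 91% at 12 months. At 10% loss, power is 79.6%. It also cites earlier recruitment of 115% of target: 576 × 1.15 = 662.4, or 18.4 per site, and 14.7 after 20% loss, for 79.9% power. Those are results from other studies and do not alter what this section claims.
- **The result below 80% depends on the reconstruction.** Partly so. With a normal approximation or an omnibus test, power stays near 81%, but those methods give about 84% at 16 per site and do not reproduce the stated figure.
- **Repeated measures, covariates and multiple imputation recover information.** They may. The gain cannot be computed from the article, and the power section itself counts missing post-tests as lost individuals.
- **The full protocol may have the detail.** The point is not that something was left out. Figures printed in the article conflict.

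A reader might go further and infer that sites would stop recruiting at 16. Nothing supports that: 576 is a target, no per-site cap is stated, and the section contemplates sites with more than 16 youths.

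**Conclusion.** The point holds as an arithmetic inconsistency. The enrolment target equals the post-loss requirement, so the 20% allowance that the section describes is not in it, and the sentence on more than 16 individuals repeats the mistake.

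The consequence is modest. With 576 enrolled, power for d = 0.48 is about 78% at 20% loss (79% with 33 df) and 79.6% at 10% loss, against a stated 80%. Equivalently, 80% power applies to d of about 0.49. These figures assume equal site sizes, ICC 0.10 and the 22-df calculation that reproduces the plan's own result.

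It would be tempting to conclude that the trial is seriously underpowered. The figures do not support that: at an ICC of 0.10 the number of sites matters much more than the number per site, and the 36 sites are unaffected by this slip.

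**What to change.** Restate the figures in one of two ways:

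1. Keep 576 as enrolment and state power of about 78% for d = 0.48 at 20% loss (80% for d of about 0.49); or
2. State that 576 is the number to be analysed, which corresponds to 720 enrolled, an average of 20 per site, at 20% loss.

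In either case, reword the sentence about more than 16 individuals so that the threshold is 16 with post-test data, i.e. 20 enrolled at 20% loss. It would also help to say whether the 20 to 80 range refers to sites or to youths per site.

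The cost is wording. Option 1 makes the stated power slightly less favourable. Option 2 makes explicit a target of 144 more youths at the same 36 sites.
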